## 2 OBJECTIVES

The primary aim of this project is to investigate the effects of combined exercise training with high mechanical loading of bones and nutritional counselling for improving bone health in wheelchair users with an initially low-normal to low BMD (Z-score  $\leq 0.0$ ). Specifically, the following objectives are to determine the effects of the intervention on:

1. Bone health, measured as changes in BMD and blood bone markers.
2. Physical health, including body composition and muscular fitness.
3. Mental health, with focus on well-being, QOL and user experience.

Our secondary aim is to use this knowledge to develop recommendations and implementation plans for exercise and nutrition to promote bone health of wheelchair users.

This is the first study worldwide to implement a long-term bone-specific exercise and nutrition program focussing on improving bone health in wheelchair users. Furthermore, including a target group of both sport active and non-active participants allows us to dig deeper into the effect of the bone-specific exercise and not only of physical activity in general. Research in this group has been underprioritized, and this project will add valuable scientific and practical information on the effects of targeted exercise and nutrition for bone health, as well as the coinciding influence on general physical and mental health of wheelchair users.

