## 4 PARTICIPANTS

### 4.1 Number of participants

Power calculation is performed using GPower 3.1. The primary outcome and focus of the RCT is change in BMD of the spine. Mean and standard deviations for a relevant difference between intervention and control group is based on a previous 24-week exercise intervention that showed a significant increase in BMD of the spine of 3.5 % (Rubin et al., 2020). Based on an 80 % power at a significance of  $P=0.05$ , the sample size needed to detect a relevant change in BMD of the spine would be 22 persons in each group. To account for a potential 35 % dropout rate, **30 participants** will be included in each group. Based on ~39% prevalence of BMD Z-score of the spine  $\leq 0$  SD in the wheelchair users in the ParaNut study (unpublished), we assume ~150 participants need to be screened. However, in order to reach this number of participants, we include wheelchair users with BMD Z-score  $<0$  at any measured site. We believe that a participant with Z-score  $>0$  at lumbar spine also could benefit from the intervention. Furthermore, as Z-scores of the hip and femur neck are secondary outcome parameters, we choose to include participants with a Z-score  $<0$  at any measured site.

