### 4.2 Inclusion criteria

Inclusion criteria are as follows: 1) BMD Z-score of any measured site  $\leq 0$  SD, 2) primary aid for mobility being a manual wheelchair, i.e.  $\geq 50\%$  of the time, 3) 18-60 Y, 4) congenital (i.e., CP, spina bifida, dysmelia, hip dysplasia) and acquired disabilities (i.e., SCI, amputation), and 5) ability to perform key exercises (e.g., overhead press).

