### 5 MEASUREMENTS

#### 5.1 Dual energy x-ray absorptiometry (DXA)

Body composition and BMD will be assessed by dual x-ray absorptiometry (Lunar iDXA, GE Healthcare, Madison, USA) in an overnight-fasted and rested state. Participants are placed on the DXA scanner in their underwear, and the procedure will last maximally 20 minutes. Whole and regional lean body mass, fat mass, and body fat percentage, as well as total body, spine, bilateral hips, femoral necks, and distal femur BMD (absolute and t- and z-scores) are analysed by the enCORE software. Trained lab engineers and researchers will perform the DXA scans and analyses.

The DXA scanning includes imaging of the whole body for determination of fat mass and fat free mass (radiation dose ~0.003-0.008 mSv). In addition, images of the lumbar spine (radiation dose ~0.005 – 0.014 mSv) and hip (radiation dose ~0.002 – 0.004 mSv) will be made for the assessment of bone density. The cumulative effective dose will be ~0.010 – 0.026 mSv. In comparison, the daily radiation dose from natural sources in Norway (cosmos, air, food, soil) is ~0.011, and the radiation dose from a one-way intercontinental flight is ~0.050 mSv. Thus, the radiation involved in this study is marginally higher than the daily radiation dose from natural sources, but substantially lower than an intercontinental flight. However, for extra caution, female participants will be asked about (planned) pregnancy. If the time between screening and test day 1 exceeds 6 weeks, an additional scan will be performed at test day 1.

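### Widening entry to a low Z-score at any site removes the implicit need for a readable spine scan, so participants can be randomized without usable data on the spine primary outcome.

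*Protocol*

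**What the plan says.** Section 4.1 states: "The primary outcome and focus of the RCT is change in BMD of the spine". It bases the screening number of about 150 on an unpublished prevalence of about 39% for a spine Z-score at or below 0. It then widens entry ("However, in order to reach this number of participants, we include wheelchair users with BMD Z-score" below 0 at any measured site) and gives three reasons: reaching the planned number, a belief that people with a lumbar spine Z-score above 0 could also benefit, and the place of hip and femoral neck among the secondary outcomes.

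Section 4.2 carries the wider rule as the first inclusion criterion: "BMD Z-score of any measured site" at or below 0 SD. Section 5.1 lists the sites as "total body, spine, bilateral hips, femoral necks, and distal femur BMD". Eligible diagnoses in section 4.2 are "congenital (i.e., CP, spina bifida, dysmelia, hip dysplasia) and acquired disabilities (i.e., SCI, amputation"). Neither section 4.2 nor section 4.3 says that the lumbar spine scan must be evaluable.

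Section 2 describes the aim as "improving bone health in wheelchair users with an initially low-normal to low BMD", with a Z-score at or below 0.0, and names no skeletal site. Section 7.1 says that the screening DXA results also serve as the pre-intervention values in the trial analysis.

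**The concern.** A spine entry rule has a useful side effect: nobody can qualify without a spine Z-score that can be read. An any-site rule loses it. A person can qualify on the hip, femoral neck, distal femur or total body while the lumbar spine scan yields no usable value. Two of the named eligible diagnoses, SCI and spina bifida, involve the spine itself.

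Such a participant fills one of the 30 places in a group but adds nothing to the primary comparison. The mixed model in section 7.1 can use incomplete outcome series, but it cannot use a participant with no spine values at all. The loss adds to dropout, and the 35% allowance in section 4.1 was made for dropout alone.

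Two lesser matters follow from the same widening. The population wording in section 2 was not adjusted, so a spine result could be read as an effect in people with low spine BMD. The figure of about 150 still belongs to the spine rule.

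**Working it through.** **Inputs from the protocol.** 30 randomized and 22 needed per group (4.1); 60 in total (4.5); spine prevalence 0.39 and about 150 to be screened (4.1); clinically low BMD in 18 of 26 wheelchair athletes (section 1, printed as 72%; 18/26 = 69%).

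**Assumed inputs.** The share of participants without an evaluable spine, u, is not in the protocol; 5% to 20% is used. The share of wheelchair users with a Z-score at or below 0 at any site, p, is also not given.

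**1. The protocol's screening figure.** 60 / 0.39 = 154, which reproduces about 150. The figure therefore rests on the spine criterion.

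**2. Usable primary-outcome data per group** = 30 × (1 − u), before dropout.

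| u (assumed) | Usable per group | Margin over 22 | Dropout that the margin absorbs |
|---|---|---|---|
| 0% | 30 | 8 | 8/30 = 27% |
| 5% | 28.5 | 6.5 | 6.5/28.5 = 23% |
| 20% | 24 | 2 | 2/24 = 8% |

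Even with u = 0 the margin falls short of the 35% dropout that section 4.1 allows for. That is a separate matter; here the point is that any u above 0 narrows it further.

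**3. Enrolled share with spine Z-score above 0.** Everyone with a spine Z-score at or below 0 passes the any-site rule, so the share is 1 − 0.39/p.

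- p = 0.39: 0%
- p = 0.50: 1 − 0.39/0.50 = 22%
- p = 18/26 = 0.692: 1 − 0.39/0.692 = 44% (26 of 60)
- p = 1.00: 1 − 0.39 = 61% (37 of 60)

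The range 44% to 61% applies only if the athlete figure in section 1 is a floor for p in the trial population. Without that, the range is 0% to 61%.

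**4. Screening number under the any-site rule** = 60/p. At p = 0.692 it is 87; at p = 1.00 it is 60. So about 60 to 87 if 69% to 100% qualify.

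**5. Threshold.** Section 4.1 uses a strict inequality for the any-site rule ("we choose to include participants with a Z-score" below 0). Sections 2 and 4.2 use at or below 0.

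**The case against.** The strongest defence is that the widening is deliberate, disclosed and reasoned. Randomization protects the arm comparison, and an average effect over the enrolled population is a valid estimate. That stands, and the any-site rule need not be withdrawn.

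The protocol also nowhere says that unreadable spine scans occur, and handling of individual vertebrae is often left to a DXA procedure or the SAP. The first part stands: the 5% to 20% is an assumption with no anchor in the text. The second part stands only for analysis. Who may be randomized is fixed in section 4.2, and a later document cannot recover a primary outcome that could not be measured.

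A reader might infer three stronger things, none of which the protocol supports:

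- **That the primary result does not answer the stated objective.** Section 2 names no site, so someone with a low hip and a spine Z-score above 0 fits its wording.
- **That about half of those enrolled will have above-average spine BMD.** This needs the any-site prevalence, which is not given. The athlete figure comes from 26 people with no stated cut-off for clinically low, while the trial also enrols non-active users.
- **That power is lost or the effect diluted through participants with higher spine BMD.** The protocol gives no figure for how response varies with baseline spine Z-score.

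The outdated screening figure is an overestimate of a logistics number and does not affect inference.

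**Conclusion.** The point holds in a limited form. The protocol measures its primary outcome at the spine but no longer ensures that the spine can be measured in those it randomizes. The gap follows directly from sections 4.1 to 4.3. Its size does not: at an assumed 5% to 20% without an evaluable spine, 30 per group becomes 28.5 to 24 before dropout, and at 0% nothing is lost. Closing the gap is a cheap improvement to a defensible design; it does not correct an invalid one.

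The wording in section 2, the two forms of the threshold and the figure of about 150 are minor consistency points. The share of participants with spine Z-score above 0 is unknown. It is 44% to 61% only if the athlete figures carry over, which is reason enough to state the population precisely but not to claim that the trial misses its objective.

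**What to change.** Keep the any-site rule and make these changes:

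1. In section 4.2, require that the lumbar spine on the screening scan be evaluable, with a short definition chosen by the sponsor, such as a minimum number of assessable vertebrae within L1-L4. In section 5.1, state that the same vertebrae are analysed at every visit.
2. In section 2, describe the population as having a Z-score at or below the threshold at one or more measured sites, so that the spine result is not read as an effect in people with low spine BMD.
3. Reconcile the strict inequality in section 4.1 with the form in sections 2 and 4.2.
4. In section 4.1, state that about 150 refers to the superseded spine rule, and give a number for the any-site rule with its assumed prevalence (about 60 to 87 if 69% to 100% qualify).

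A baseline spine Z-score by treatment interaction is optional. With 60 randomized it would be imprecise and should be labelled exploratory.

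The cost is protocol wording. The screening scan is already performed, so no visit or measurement is added. The downside is that a few screened people without an evaluable spine become ineligible.

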### 4.2 Inclusion criteria

Inclusion criteria are as follows: 1) BMD Z-score of any measured site  $\leq 0$  SD, 2) primary aid for mobility being a manual wheelchair, i.e.  $\geq 50\%$  of the time, 3) 18-60 Y, 4) congenital (i.e., CP, spina bifida, dysmelia, hip dysplasia) and acquired disabilities (i.e., SCI, amputation), and 5) ability to perform key exercises (e.g., overhead press).

### 4.3 Exclusion criteria

Exclusion criteria: 1) spinal cord injury acquired  $<2$  Y ago; 2) known problems with autonomic dysreflexia (see attachment “SOP Pre-screening telefonsamtale”) 3) menopause; 4) change in health and/or medication within the last 3 months, 5) fracture within the last 6 months, 6) pregnancy or planned pregnancy during the study period; 7) language or cognitive barriers affecting the ability to understand all aspects of the study, 8) patients with progressive neurological disease, serious or uncontrollable epilepsy, endocrine diseases (including diabetes mellitus type 1 or 2, thyroid disorders, calcium homeostasis disorders and metabolic bone disease, pituitary gland disorder, sex hormone disorders), cancer, serious mental disorder, or comorbid medical conditions affecting either a) nutritional function: i.e., malabsorption problems due to previous surgery in the gastrointestinal tract, inflammatory bowel disease, coeliac disease, eating disorders, chronic pancreatitis, liver or kidney disease (those that cannot convert vitamin D to its active form in the body), other conditions affecting vitamin D or calcium absorption; b) musculoskeletal system: i.e., congenital systemic skeletal dysplasia affecting bone density, inflammatory arthritis conditions (such as rheumatoid arthritis, psoriatic arthritis, ankylosing spondylitis, and lupus), ongoing tendinitis or muscle injuries not compatible with the exercise intervention; c) cardiovascular system: i.e. congenital heart failure, congenital connective tissue disorders affecting the aorta and/or arteries, other cardiovascular conditions not compatible with the exercise intervention; 9) the use of certain medications: bisphosphonates, PTH (teriparatide), Denosumab, Raloksiphen, Prednisolone/steroids/androgenic steroids, high dose oestrogen (including medroxyprogesterone acetate contraceptives) immunosuppressive medications/ chemotherapies, vitamin K, anti-epileptic medication (Lamotrigine, Phenytoin, Phenobarbital, Carbamazepine, Primidone), proton pump inhibitors (PPIs), selective serotonin receptor inhibitors (SSRIs), thiazolidinediones (TZDs), anticonvulsants, hormone deprivation therapy, calcineurin inhibitors, and isotretinoin; 10) other therapies that aim to increase bone mineral density, e.g., vibration therapy, functional electrical

stimulation (FES); 11) alternative medicine that interfere with vitamin D or calcium metabolism or affect bone mineral density, 12) known other contraindication of resistance exercise.

#### 4.4 Recruitment

Potential candidates will receive oral and written information on all study procedures and assessments from PhD Candidate [name]. The participant information document (attachment D1) will be distributed to all national project partners for use in recruitment. We aim to contact local (to the three sites) newspapers, as well as larger papers/online papers and websites such as forskning.no, to get the study featured. Further, recruitment will be sought directly through rehabilitation centres, such as Sunnaas Rehabilitation hospital, and user organisations such as Landsforeningen for Ryggmargskadete (LARS) and their platforms such as member magazines/newsletters. Lastly, we aim to recruit wheelchair Para athletes through the Norwegian Olympic and Paralympic Committee and Federation of Sports. We will present the project at a breakfast meeting for coaches and staff of Para athletes October 2022.

#### 4.5 Randomization

Based on physical activity level, each participant will be categorized as non-active, moderately active, and very active (see 5.6 Questionnaires). Eligible participants will be randomly assigned to one of the two study groups, an intervention group (n=30) or a control group (n=30). The randomization list will be created using Randomizer.org, and stratified by physical activity status, sex, and SCI/non-SCI, with a 1:1 allocation using random block sizes of 4, 6, and 8. To ensure allocation concealment, we will use sequentially numbered, non-transparent envelopes containing the treatment allocation information. The groups will be checked for distribution of age, medication use, degree of injury/disability, and degree of wheelchair use.

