## 3 STUDY DESIGN

This multi-site study is a 24-week exercise intervention in which the participants also will receive nutritional optimization for bone remodelling. In this randomized controlled trial, interested participants will attend the lab at NIH, Western Norway University of Applied Sciences (HVL) or Norwegian University of Science and Technology (NTNU) for screening prior to being included and invited back for baseline testing. Subsequent randomization for the intervention or control group will be performed (see 4.5 Randomization). Supervised training in the initial four weeks of the intervention will be conducted on-site (NIH, HVL, NTNU), followed by monthly on-site sessions and off-site follow up with the intervention group. Nutritional optimization for bone remodelling will be provided to both groups. Repeated testing at the intervention midpoint and end of intervention aims to investigate the effect of the intervention.

[figure not shown]

**Figure 2: Schematic overview of the BoneWheel study.** Screening based on participant criteria will include eligible participants to progress to baseline testing and further to the randomized controlled trial. Images represents the test battery; Dual-energy X-ray Absorptiometry, questionnaires, physical tests (strength, rate of force development, function), blood sample, 24h dietary recall.

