## 6 INTERVENTION

Based on the inclusion criteria screened participants will be invited to participate in the intervention. After attending the baseline testing, the participants are randomized into the intervention or control group. All testing is conducted at NIH, HVL or NTNU based on the participants living location.

[figure not shown]

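### Twelve strata for 60 participants, with blocks of 4, 6 and 8, leave most blocks unfilled, so the stated 30/30 split is not secured; the harm is modest and the repair is cheap

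*Protocol*

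**What the plan says.** Protocol section 4.5 (Randomization) states that "each participant will be categorized as non-active, moderately active, and very active", and that the list will be "stratified by physical activity status, sex, and SCI/non-SCI, with a 1:1 allocation using random block sizes of 4, 6, and 8". The arms are given as "an intervention group (n=30) or a control group (n=30"). Allocation uses sequentially numbered opaque envelopes. After allocation the groups are checked for the distribution of age, medication use, degree of injury or disability, and degree of wheelchair use; no action is attached to that check.

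Section 3 has participants "attend the lab at NIH, Western Norway University of Applied Sciences (HVL) or Norwegian University of Science and Technology (NTNU"), and section 6 adds "All testing is conducted at NIH, HVL or NTNU based on the participants living location". Site is not a stratification factor.

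Section 4.1 says that the number needed "would be 22 persons in each group", raised to 30 for dropout. Section 7.1 names time, treatment and their interaction as the fixed effects of the mixed model.

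**The concern.** Permuted blocks force equal numbers only when a block is filled. A stratum that stops mid-block carries a chance surplus in one arm, and these surpluses add up across strata. With many strata and few people in each, stratified blocking gradually loses the balance in overall group size that it is used to obtain.

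Here the average stratum is smaller than the average block. At stake are the stated group sizes and, to a lesser degree, the even split of the factors that the sponsor chose to balance.

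**Working it through.** **Inputs.** From Protocol section 4.5: 3 activity levels, 2 sexes, SCI yes/no, blocks of 4, 6 and 8, and 30 per arm. From section 4.1: 22 evaluable per arm, 80% power, P = 0.05 (taken as two-sided) and 35% dropout. The protocol gives no stratum shares and no probabilities for the block sizes. I assume equally likely block sizes and vary the shares from an even mix to activity 20/30/50%, sex 75/25%, SCI 80/20%.

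**The plan's own figure.** 22 × 1.35 = 29.7, rounded up to 30 per arm, so 60 in total.

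**Strata and blocks.** 3 × 2 × 2 = 12 strata; 60/12 = 5 per stratum; mean block (4 + 6 + 8)/3 = 6.

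**Chance that a stratum ends on a filled block.** It is zero for 1–3 people and for any odd number. Otherwise:
- size 4 or 6: 1/3 = 33%
- size 8: 1/3 + 1/9 = 44%
- size 10: 2/9 = 22%
- size 12: 3/9 + 1/27 = 37%

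**Strata ending mid-block (simulation).** 10.2 of 11.9 non-empty strata with even shares, 10.1 of 11.4 with moderately uneven shares and 9.4 of 10.5 with very uneven shares; that is 86–90%.

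**Balance (simulation of 60 participants; ranges span the assumed shares).**

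| Scheme | Exactly 30/30 | 33/27 or worse | SCI count differs by 4 or more | SCI share differs by more than 15 points | Some activity level's share differs by more than 15 points |
|---|---|---|---|---|---|
| Protocol: 12 strata, blocks 4/6/8 | 20–22% | 16–21% | 20–21% | about 3% | 3–5% |
| Simple randomisation | about 10% | 51–52% | 52–62% | 14–24% | about 42% |
| 12 strata, blocks 2/4 | about 27% | 7–9% | 7–9% | – | – |
| Minimisation (activity, sex, SCI, site; preferred arm with probability 0.8) | – | under 1% | 4–5% | – | about 3% |

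**Reading the SCI count.** The count partly reflects unequal arm sizes. Suppose 36 of 60 have SCI and they split 20/16. With arms of 30/30 the shares are 20/30 = 66.7% and 16/30 = 53.3%, 13 points apart. With arms of 32/28 they are 20/32 = 62.5% and 16/28 = 57.1%, 5 points apart. The difference in share is the better measure of possible confounding.

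**Power cost of unequal arms.** The protocol gives no SD, but 22 per arm at 80% power implies a standardised effect of about 0.865. Relative to equal arms, the noncentrality is multiplied by √(4·n₁·n₂/N²).
- 22/22: factor 1, power 80.0%
- 25/19: √(1900/1936) = 0.991, power 79.3%
- 26/18: √(1872/1936) = 0.983, power 78.7%

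**The case against.** The strongest reply is that little follows from this. Stratified blocking still does most of its work: large differences in SCI share are rare, those in sex equally so (more than 15 points in 2.7% of trials, against 24% under simple randomisation), and the power loss is about 1 point. That reply stands and sets the weight of the point.

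Several stronger readings are tempting, and the documents do not support them.

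- *Balance on SCI and sex is not delivered.* Raw counts suggest this, but the shares show balance that is imperfect and largely achieved.
- *SCI imbalance would bias the primary result.* The background section describes low bone density in wheelchair users generally and notes that most research was done in SCI. It gives no effect of SCI on 24-week change in spine bone density, which is the primary outcome.
- *Three sites triple the number of sequences.* Section 4.5 speaks of one list, and nothing says that lists or envelopes are held per site.
- *Activity should be dropped to reduce the strata.* This would raise the chance that some activity level's share differs by more than 15 points from 4–5% to about 40%. Section 2 treats the mix of sport-active and non-active participants as central, and section 5.6.1 says that the activity questionnaire is used to stratify.
- *The model wrongly omits the stratification factors.* Such adjustment is often specified in a statistical analysis plan, which is not at hand, so its absence from section 7.1 is not a fault in itself.

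**Conclusion.** The point holds as a modest design weakness. The protocol combines 12 strata, 60 participants and blocks averaging 6, so about 10 strata end mid-block. The stated 30/30 split is reached in about one trial in five, and 33/27 or worse occurs in about 16–21%. These figures rest on assumed stratum shares and equally likely block sizes, but they change little across the mixes tried.

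This does not threaten the trial's validity. It is worth correcting because a better allocation method exists at small cost and gives up none of the factors that the sponsor wants balanced.

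**What to change.** **Preferred.** Keep activity level as a balancing factor. Allocate all participants not yet randomised centrally, by minimisation with a random element over activity, sex, SCI status and site. In simulation this cuts 33/27 or worse to under 1% and SCI count differences of 4 or more to about 4–5%, with activity balance at least as good as now. It also brings site into the balance, which the present scheme leaves to chance. The cost is a central allocation procedure in place of pre-filled envelopes, and an amended paragraph in section 4.5.

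**If envelopes must stay.** Keep the 12 strata and use smaller blocks. Blocks of 2 and 4 bring both measures to about 7–9%. The cost is a new list and somewhat greater predictability, which matters because participants know whether they have been assigned to train; block sizes should not be disclosed to those enrolling.

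**In either case.** Add the balancing factors as fixed effects to the mixed model in section 7.1, unless the statistical analysis plan already does so. This needs one sentence and no extra data collection.
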